#### Phase 2: Cluster Randomized Controlled Trial

Building on the results of phase 1, this phase will expand to include the ICUs of FJCUH and MSGH, conducting a cluster randomized controlled trial from January 1, 2026, to December 31, 2027, to evaluate the practical application of the CAD system in a multicenter setting, as well as to assess clinical and economic benefits. In addition, the attending physicians, residents, and specialized nurses in the ECC and ICUs will sign consent forms, which will allow them to use the CAD system. Patients will be exempted from providing informed consent, as the study poses minimal risk, and the potential risks for participants are no greater than those for nonparticipants. Exempting informed consent will not affect their rights. The inclusion and exclusion criteria are shown in Textbox 2.

The study will use cluster randomization, stratified by ventilator use frequency, to balance the risk of pneumothorax between the 2 groups and reduce potential confounding bias. Within each stratum, the ventilator use will be similar, while the difference in use between strata will be larger. A uniform distribution will be applied to assign each ward unit a random probability. On the basis of these probabilities, the units will be ranked and assigned to either the intervention or control group based on their odd or even rank.

In the control group, physicians will continue with the current diagnostic process and will not be able to view the model’s predictions. In the intervention group, physicians will be authorized to access the AI model’s predictions during patient care as an additional decision-making reference. These predictions will be generated in seconds and can help identify issues such as tube misplacement (eg, NGT and ETT) and pneumothorax through AI analysis of CXRs, which will alert the physician to review the images. Access to the model’s prediction interface was restricted to physicians in the intervention group, with access for the control group technically disabled through role-based permissions within the hospital information system. This measure ensured that physicians in the control group were not exposed to any AI-generated outputs. In addition, to promote consistent use of the CAD system within the intervention group, log-in records will be monitored, and reminders will be issued in cases of noncompliance.

Data collection included the total number of patients in the ward, the number of patients using ventilators, the number of pneumothorax cases, CXR results, misplacement detection time, mortality rate, length of stay, ETT resetting time, NGT resetting time, pneumothorax drainage tube placement time, direct medical costs (eg, x-ray examinations, intubation fees, and hospitalization fees), and indirect medical costs (eg, CAD system costs and labor costs). The implementation costs are expected to differ between the intervention and control arms. The intervention arm includes additional expenditures related to AI system deployment, such as system infrastructure, routine maintenance, training, and IT support. These costs are captured as part of the economic evaluation to assess whether the clinical benefits of AI-assisted care justify the associated investment. Imaging data will not be collected, and the AI software will not undergo model training.

The inclusion and exclusion criteria for cluster randomized controlled trial.

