**Figure 2 figure2:**
[figure not shown]
Summary of the model for pneumothorax detection. (A) Original image. (B) Boundary boxes (green rectangles) and segmentation masks (red regions) after preprocessing by the detection and segmentation model systems. (C) Boundary boxes (red rectangles) predicted by the detection model system. (D) Segmentation masks (purple regions) predicted by the segmentation model system.

The AI-based computer-aided diagnostic system automatically detects and assesses catheter placement and pneumothorax, providing excellent prejudgment capabilities for potentially misplaced catheter images. It reduces delays between obtaining CXR images and clinical interpretation, thus improving clinician efficiency. This, in turn, helps to reduce adverse reactions from catheter misplacement and subsequent management of pneumothorax, thereby improving patient prognosis and reducing complications.

This study focuses on the clinical validation and deployment of this system rather than on algorithm development or segmentation metrics. Although several foundational studies involving segmentation performance and metrics such as the Dice coefficient were conducted within the NTUH health care system, this trial aims to extend the findings and tools developed in those earlier studies to a broader range of health care settings. To enhance the generalizability and applicability of the research across institutions with varying levels and organizational structures, we have included 3 participating sites: a medical center (NTUH), and 2 regional hospitals (Fu Jen Catholic University Hospital [FJCUH] and Min-Sheng General Hospital [MSGH]).

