## Methods

### Research Design

This study adopts a 2-phase design, beginning with a pilot study followed by a multicenter cluster randomized clinical trial. The pilot phase focuses on integrating a CXR CAD system into the hospital’s medical information systems, ensuring smooth functionality within the clinical workflow. The system will undergo testing and initial evaluations in the emergency intensive care and ICU at NTUH over a period of 6 to 12 months.

Building on the pilot phase, the multicenter clinical trial involves ICUs from NTUH, FJCUH, and MSGH. A total of 18 ICU units will participate, with NTUH contributing 14 units and the remaining hospitals contributing 2 units each. These units will be randomized into AI-assisted and control groups. Stratification is based on ventilator use, with randomization conducted within each stratum using uniform distribution. The AI-assisted group allows physicians to access real-time predictions from the CAD system during patient care. These predictions, generated within seconds, focus on identifying critical conditions, such as NGT misplacement, ETT misplacement, and pneumothorax. However, physicians in the control group will adhere to standard procedures without viewing AI-generated predictions, though the CAD system will still analyze images for internal validation. To minimize potential bias, both the outcome assessors and data analysts will remain blinded to group allocation throughout the data collection and statistical analysis phases.

The primary outcome is patient all-cause mortality rate: Assess whether the in-hospital mortality rate decreases after the intervention, reflecting the AI-assisted detection system’s ability to identify life-threatening conditions in a timely manner and facilitate rapid clinical intervention.

The secondary outcomes are as follows:

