### Determination of Sample Size

The primary outcome of the trial is to assess whether the CAD system can reduce in-hospital mortality. On the basis of data from the NTUH institutional database [19], the ICU mortality rate in 2023 to 2024 is estimated at 28%. A projected reduction to 25% was used for the sample size calculation. With an intraclass correlation coefficient of 0.01, a power of 80%, and a 1-sided α of 5%, each group requires 5450 patients, resulting in a total sample size of 10,900. This design is expected to provide sufficient power to detect clinically significant improvements in patient outcomes (Figure 3).

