### Statistical and Cost-Effectiveness Analysis

Statistical analysis will be conducted using SAS software (SAS Institute) to evaluate the outcomes of this study. Continuous variables, such as clinical outcomes and procedural times, will be summarized using descriptive statistics, including the number of observations, mean, median, SD, range, and 95% CIs. For categorical variables, frequency counts and percentages will be used to summarize the data.

In terms of clinical effectiveness, the primary outcome will be in-hospital mortality, and a proportional test will be used to compare the mortality rates between ICUs that have implemented the AI-assisted detection system and those that have not. The secondary clinical outcomes, which include the length of stay in the hospital, time to detect tube misplacements, and the time taken for medical interventions (such as repositioning of ETT and NGT and placement of pneumothorax drainage), will be analyzed using *t* tests for continuous variables. For categorical outcomes, including the rates of misplacement and other related interventions, chi-square test will be used. In addition, proportional tests will be conducted to examine the differences in the frequency of interventions across the 2 groups.

The study will also incorporate a health care technology and economic evaluation framework to assess the cost-effectiveness of the AI system alongside its clinical effectiveness. This evaluation will explore whether the clinical benefits derived from the AI system justify the associated resource consumption. Previous research by the team [21], such as the use of Markov models in gastric cancer screening and prevention, has demonstrated the utility of such economic evaluations, particularly in quantifying the cost-effectiveness of medical interventions and their impact on mortality reduction.

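### Allocation is stratified by ventilator use but not by hospital, so a regional hospital's two units may well land in the same arm, an avoidable chance imbalance

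*Protocol article*

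**What the plan says.** The stratification factor is given twice. Research Design has: "Stratification is based on ventilator use, with randomization conducted within each stratum using uniform distribution". Phase 2: Cluster Randomized Controlled Trial has: "The study will use cluster randomization, stratified by ventilator use frequency, to balance the risk of pneumothorax between the 2 groups". Within a stratum each unit receives a uniform random number, and "the units will be ranked and assigned to either the intervention or control group based on their odd or even rank". Nothing in the article stratifies, blocks, matches or constrains by hospital, and the number and size of the ventilator strata are not given.

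On the clusters, Research Design says: "A total of 18 ICU units will participate, with NTUH contributing 14 units and the remaining hospitals contributing 2 units each". The last paragraph of Prior Work describes the sites as "a medical center (NTUH), and 2 regional hospitals" and says that the mix was chosen to make the results apply to institutions of different level and organisation.

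For the primary outcome, Statistical and Cost-Effectiveness Analysis says that "a proportional test will be used to compare the mortality rates between ICUs that have implemented the AI-assisted detection system and those that have not".

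**The concern.** With 18 clusters, randomisation cannot be relied on to even out a factor that is carried by only two or four of them. The article itself treats the three hospitals as different in kind, yet the one factor balanced by design is ventilator use. If both units of a regional hospital fall in the same arm, two things follow. That hospital contributes no comparison of CAD with standard care under its own roof, which weakens the purpose for which the regional sites were added. In addition, any difference in baseline mortality, length of stay or cost between that hospital and the rest enters the crude arm difference. Adjustment at the analysis stage can soften the second consequence but cannot undo the first.

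**Working it through.** **Inputs.** From Research Design: 18 units, of which NTUH has 14, FJCUH 2 and MSGH 2 (14 + 2 + 2 = 18, so the count is consistent). From the Phase 2 section: allocation by odd or even rank within a stratum, hence about 1:1. From Determination of Sample Size: 28% against 25%, a planned effect of 3 points. The strata and any between-hospital mortality difference are not given, so both are treated as assumptions below.

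**One stratum of 18, 9 units per arm.** There are C(18,9) = 48,620 equally likely allocations.
- A given regional hospital has both units in one arm: 2 × C(16,7) / C(18,9) = 22,880 / 48,620 = 0.47 (equivalently 8/17).
- Both regional hospitals are split: 4 × C(14,7) / C(18,9) = 13,728 / 48,620 = 0.28. At least one is therefore unsplit with probability 1 − 0.28 = 0.72.
- All four regional units are in one arm: 2 × C(14,5) / C(18,9) = 4,004 / 48,620 = 0.08.

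**Several strata.** If a hospital's two units share a stratum of even size s, they land in the same arm with probability (s/2 − 1)/(s − 1). This is 0.44 for s = 10, 0.43 for 8, 0.40 for 6, 0.33 for 4 and 0 for 2. If they sit in different even-sized strata, it is 0.50. The joint events below come from 100,000 simulated draws of the odd/even rule per layout (the first row agrees with the exact values above).

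| Layout of strata and regional units | Given hospital unsplit | At least one unsplit | All four in one arm |
|---|---|---|---|
| One stratum of 18 | 0.47 | 0.72 | 0.08 |
| 9 + 9, all four in one stratum | 0.44 | 0.68 | 0.05 |
| 9 + 9, each hospital's units in different strata | 0.51 | 0.75 | 0.11 |
| 10 + 8, all four in the 8 | 0.43 | 0.66 | 0.03 |
| 6 + 6 + 6, all four in one stratum | 0.40 | 0.60 | 0 |
| 6 + 6 + 6, one hospital in each of two strata | 0.40 | 0.64 | 0.08 |
| 6 + 6 + 6, each hospital's units in different strata | 0.50 | 0.74–0.75 | 0.08–0.10 |
| 4 + 4 + 4 + 6, all four in one stratum of 4 | 0.33 | 0.33 | 0 |
| 4 + 4 + 4 + 6, one hospital in each of two strata of 4 | 0.33 | 0.55 | 0.06 |
| Nine pairs, one hospital forming a pair, the other across two pairs | 0 and 0.50 | 0.50 | 0 |

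If the four units lie in four different even-sized strata, the values are 1 − (1/2)² = 0.75 for at least one unsplit and 2 × (1/2)⁴ = 0.125 for all four together. A hospital is certain to be split only when its two units form a stratum of their own.

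**Effect on the arm difference.** Assume equal unit sizes, 9 units per arm, and a hospital whose mortality differs from the rest by D points. With both its units in one arm, it makes up 2/9 of that arm and none of the other, so the crude difference shifts by 2D/9. For D = 3, 5 and 10 the shift is 0.7, 1.1 and 2.2 points. If all four regional units share an arm and both hospitals differ by D, the shift is 4D/9, which is 1.3, 2.2 and 4.4 points. The planned effect is 3 points.

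**The case against.** Several points on the other side are sound.

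- Allocation is random, so an unsplit hospital is chance imbalance and not bias in expectation. A reader might infer that the CAD effect of the whole trial would be confounded with hospital. The documents do not support that: with 9 units per arm, NTUH's 14 units cannot fit into one arm, so most of the comparison is made within NTUH. Separation is complete only inside an unsplit regional hospital.
- The article gives no mortality difference between hospitals. It says only that they differ in level, and its 28% comes from NTUH alone. The shifts above are therefore conditional. They can also be set against ordinary between-unit noise: the plan's ICC of 0.01 implies a between-unit SD of √(0.01 × 0.28 × 0.72) = 4.5 points, hence a standard error of 4.5 × √(2/9) = 2.1 points for the arm difference. A shift of 1.1 points is about half of that.
- A reader might also infer that the odd/even rule must give unequal arms, for instance 10 against 8 from two strata of 9. That needs odd-sized strata and the same parity mapped to CAD in each. The article states neither.
- Adjustment for hospital may sit in a statistical analysis plan that is not shown, so its absence from the article is not counted here. It could not, however, create a within-hospital contrast where both units share an arm.
- Forcing a split could raise contamination if the same staff cover both units, and the documents do not say whether they do. But NTUH already runs both arms under role-based access, and the present rule would split each regional hospital about half the time or more.

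These points limit the size of the problem. They do not remove it, because the omission of hospital is a stated design choice that the article nowhere contradicts.

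**Conclusion.** The point holds as a likely and avoidable chance imbalance. Under a single stratum, a given regional hospital is unsplit with probability 0.47, at least one is unsplit with probability 0.72, and all four units share an arm with probability 0.08. Because the strata are unspecified, the working ranges are about 0.33 to 0.50 per hospital (0 only if its units form their own stratum), 0.33 to 0.75 for at least one, and roughly 0 to 0.12 for all four. The firm consequence is the loss of any within-hospital CAD contrast at a site included for generalisability. The effect on the primary comparison is partial: about 0.7, 1.1 or 2.2 points for one unsplit hospital, given assumed hospital differences of 3, 5 or 10 points, equal unit sizes and 9 units per arm. This does not threaten the trial's validity, but it cannot be repaired once the allocation is in use.

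**What to change.** Before the allocation list is drawn, make FJCUH and MSGH each a stratum of two units. The existing odd/even rule then always gives one unit per arm at each, and the probability of an unsplit regional hospital falls to 0. Keep ventilator-use strata within NTUH's 14 units, preferably of even size, so that NTUH divides 7:7 and the trial 9:9. If odd-sized strata are unavoidable, randomise in each stratum which parity receives CAD. Account for hospital and ventilator stratum in the analysis.

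The cost is a changed randomisation list ahead of the January 2026 start of phase 2. There is a small downside: the four regional units are matched on hospital rather than on ventilator use. One unit against one unit improves balance but does not by itself estimate a site-specific CAD effect, since unit and CAD remain inseparable there, and the report should not claim otherwise. The sponsor should also confirm whether staff cover both units at the regional hospitals.

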**Units**
Inclusion criteriaEmergency critical care or intensive care units at National Taiwan University Hospital, Fu Jen Catholic University Hospital, and Min-Sheng General Hospital.The units included the patients requiring chest x-rays due to endotracheal intubation, nasogastric tube insertion, or ventilator use with a risk of pneumothorax.Exclusion criteriaThe unit supervisor does not agree to participate in the trial.The unit is unable to implement the artificial intelligence–assisted system (eg, no data connection or system support).
**Patients**
Inclusion criteriaPatients who are adults and require chest x-ray due to one of the following conditions: endotracheal intubation, nasogastric intubation, or the use of a ventilator with the potential to cause pneumothorax.Exclusion criteria for patients in isolation wards or pediatric wardsPatients in isolation wardsPatients in infant intensive care unit

### AI Detection Tool

The CXR real-time CAD system is an AI-assisted diagnostic software in medical devices. It uses AI algorithms to analyze bedside CXR images and detect conditions such as malpositioned NGTs, ETTs, and pneumothorax. The system provides immediate feedback on detection results and notifies the physician to review the images for confirmation. If a tube misplacement is identified, the physician can promptly adjust its position; if pneumothorax is detected, the physician can provide appropriate treatment, such as chest tube drainage.

This system is classified as a medical device software under Taiwan’s Food and Drug Administration’s “Artificial Intelligent/Machine Learning-Based Software as a Medical Device, AI/ML-Based SaMD” regulations. It uses clinical data, such as images and biochemical markers, to autonomously learn and adjust its performance through AI programming. The outputs from the analysis are not intended to manage clinical treatments but provide immediate feedback to clinicians for timely interventions or treatments. The system’s data are sourced from patient examination files stored in the database and do not involve any invasive procedures.

### Data Integration Workflow

The workflow (Figure 4) ensures seamless data exchange between the AI server and the hospital’s medical information system, optimizing the use of AI in clinical decision-making. After CXR images are acquired, they are sent to the AI server via the QC workstation. To maintain data integrity, the system has a fail-safe mechanism: if transfer issues occur, the AI server queries or retrieves the images from the integrated information system or initiates a backup retrieval process directly. Once the AI server processes the images, critical findings are identified, and alerts are generated through the hospital’s internal messaging system, improving response times for urgent cases.

Health care professionals can access images and AI-generated annotations through SoliPACS by activating the “tool” feature. In addition, physicians can provide feedback on the AI’s diagnostic accuracy, facilitating model refinement. For research purposes, workflow configuration to enable AI access rights must be requested by ward physicians and specialist nurse practitioners in relevant departments.

**Figure 4 figure4:**
[figure not shown]
Data transmission flowchart for artificial intelligence (AI) server and medical information–system integration. BLE: Bluetooth low energy; CR: computed radiography; CT: computed tomography; DX: digital radiography; IP: internet protocol; PACS: picture archiving and communication system; TCP: transmission control protocol.

### AI Computation Architecture

The system uses a file exchange method to handle the transfer of DICOM files and output data (Figure 5). Batch processing capabilities allow users to process multiple images simultaneously by placing them in the “Inputs” folder. Built on an Inference Server architecture, the system loads the AI models into memory at container activation, eliminating the need to reload models for each operation. This architecture enhances computational efficiency, particularly for high-throughput image analysis. Critical alerts and findings are displayed in real time within the hospital’s information system, ensuring a streamlined workflow for health care providers.

**Figure 5 figure5:**
[figure not shown]
Artificial intelligence (AI) computing architecture diagram. EPS: EBM PACS Server.

### Statistical and Cost-Effectiveness Analysis

Statistical analysis will be conducted using SAS software (SAS Institute) to evaluate the outcomes of this study. Continuous variables, such as clinical outcomes and procedural times, will be summarized using descriptive statistics, including the number of observations, mean, median, SD, range, and 95% CIs. For categorical variables, frequency counts and percentages will be used to summarize the data.

In terms of clinical effectiveness, the primary outcome will be in-hospital mortality, and a proportional test will be used to compare the mortality rates between ICUs that have implemented the AI-assisted detection system and those that have not. The secondary clinical outcomes, which include the length of stay in the hospital, time to detect tube misplacements, and the time taken for medical interventions (such as repositioning of ETT and NGT and placement of pneumothorax drainage), will be analyzed using *t* tests for continuous variables. For categorical outcomes, including the rates of misplacement and other related interventions, chi-square test will be used. In addition, proportional tests will be conducted to examine the differences in the frequency of interventions across the 2 groups.

The study will also incorporate a health care technology and economic evaluation framework to assess the cost-effectiveness of the AI system alongside its clinical effectiveness. This evaluation will explore whether the clinical benefits derived from the AI system justify the associated resource consumption. Previous research by the team [21], such as the use of Markov models in gastric cancer screening and prevention, has demonstrated the utility of such economic evaluations, particularly in quantifying the cost-effectiveness of medical interventions and their impact on mortality reduction.

Cost-effectiveness analysis will be conducted using TreeAge software to compute the incremental cost-effectiveness ratio. This ratio will assess the additional cost required to achieve one unit of clinical benefit when using the AI system as compared to traditional methods. The incremental cost-effectiveness ratio will be calculated by dividing the cost of the intervention (which includes the medical, AI system, and maintenance costs) by the effectiveness, which will be measured through various clinical outcomes, such as reduced diagnostic time, decreased mortality rates, fewer misdiagnoses, and quality-adjusted life years (QALYs).

QALYs will serve as a composite measure of health outcomes by combining both the quantity and quality of life. The calculation of QALYs will involve multiplying the expected survival years after the intervention by a health state weight, which reflects the patient’s quality of life during those years. This weight ranges from 0 (death) to 1 (perfect health), and negative values may be used to indicate health statuses worse than death.

QALY = Years of Life × Health State Weight

To ensure the robustness of the findings, sensitivity analyses will be conducted, including both simple sensitivity analysis and probabilistic sensitivity analysis. These analyses will account for variability in model parameters and simulate different combinations of parameters to evaluate the stability of the cost-effectiveness conclusions. The results of these analyses will be assessed through acceptance curves and cost-effectiveness planes, which will allow a comparison of the cost-effectiveness of different treatment strategies under various assumptions.

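### The named primary test has no term for the ICU or the ventilator-use stratum; a clustered analysis should carry the stratum and, if obtainable, each unit's prior mortality

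*Protocol article*

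**What the plan says.** Protocol article, Phase 2: Cluster Randomized Controlled Trial: "The study will use cluster randomization, stratified by ventilator use frequency, to balance the risk of pneumothorax between the 2 groups". Within a stratum, each unit draws a uniform random number, and "the units will be ranked and assigned to either the intervention or control group based on their odd or even rank". Research Design gives the number of clusters: "A total of 18 ICU units will participate, with NTUH contributing 14 units and the remaining hospitals contributing 2 units each". The number of strata is not stated.

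Statistical and Cost-Effectiveness Analysis names the primary analysis: "the primary outcome will be in-hospital mortality, and a proportional test will be used to compare the mortality rates" of ICUs with the system and ICUs without it. It mentions no ICU term, stratum term or baseline covariate. The secondary outcomes get t tests, chi-square tests and proportional tests, again without such terms.

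Prior mortality appears only under Determination of Sample Size. "On the basis of data from the NTUH institutional database", a single ICU mortality rate of 28% for 2023 to 2024 is given. There is no rate by unit, and none for the two regional hospitals, which supply 4 of the 18 units.

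**The concern.** The design uses ventilator use to form strata, and the named analysis then drops it. Two things follow, in this order.

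The first is validity. A two-group test of proportions on patients has a binomial standard error, which contains no between-ICU variance. With about 600 patients per ICU, even a small ICC makes that error far too small.

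The second is precision. After clustering is dealt with, the standard error is mostly between-ICU variance. Stratified allocation removes part of that variance from the treatment contrast, but an analysis without the stratum still counts it as noise. The same holds for any ICU-level predictor of mortality known before the trial. With about 9 units per arm there is little precision to give away.

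**Working it through.** **Inputs.** From Determination of Sample Size: 28% versus 25%, ICC 0.01, one-sided α 5%, power 80%, 5450 patients per arm. From Research Design: 18 ICUs. My assumptions: 9 units per arm, equal cluster sizes, no loss of patients.

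**The plan's own figure.** Individually randomised, 28% versus 25% needs 2675 per arm (2742 with continuity correction). Then 5450/2675 = 2.04 and 5450/2742 = 1.99. With a design effect of 1 + (m − 1) × 0.01, these imply m of about 105 or 100 patients per ICU. The stated 18 ICUs give m = 10,900/18 = 606, so 5450 is not reproduced with 18 clusters.

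**Design effect with 18 ICUs.** 1 + (605.6 − 1) × 0.01 = 7.05. It splits into a within-ICU part, 1 − 0.01 = 0.99, and a between-ICU part, 605.6 × 0.01 = 6.056. The between-ICU share is 6.056/7.05 = 86%.

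**Patient-level test.** With mean mortality 0.265:
- Binomial SE = √(2 × 0.265 × 0.735/5450) = 0.00845.
- SE allowing for clusters = 0.00845 × √7.05 = 0.0224, which is 2.65 times as large.
- Actual one-sided type I error = 1 − Φ(1.645/2.65) = 1 − Φ(0.62) = 27%, before any gain from the stratified allocation.

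**Chance imbalance between arms.** The between-ICU SD is √(0.01 × 0.265 × 0.735) = 4.4 points. The chance difference in underlying mortality between two arms of 9 ICUs has SD 4.4 × √(2/9) = 2.1 points, again before any gain from stratification. The target effect is 3 points.

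**Power once clustering is handled.** Let r be the correlation of the covariates with underlying ICU mortality, so that they explain r² of the between-ICU variance. The design effect becomes 0.99 + 6.056 × (1 − r²). Power comes from a noncentral t with noncentrality 0.03/SE, with 16 df unadjusted and 14-15 df adjusted.

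| r (assumed) | Design effect | SE | Power |
|---|---|---|---|
| unadjusted | 7.05 | 0.0224 | 36% |
| 0.3 | 6.50 | 0.0216 | 37-38% |
| 0.5 | 5.53 | 0.0199 | 42% |
| 0.6 | 4.87 | 0.0187 | 45-46% |
| 0.8 | 3.17 | 0.0150 | 60% |

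**Cost if the covariates explain nothing.** Going from 16 to 14 df lowers power from 35.8% to 35.5%.

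**What 80% would take.** About 74% of the total variance of an ICU's mortality proportion must be explained. That is 0.74/0.86 = 86% of the between-ICU part, or r of about 0.93 on the scale of the table.

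**The case against.** The strongest objection is that covariate choice usually belongs in the statistical analysis plan, which is not shown, and that a condensed article need not list it. This holds for prior mortality: its absence contradicts nothing in the document. It does not hold for the test itself. The article names a specific method for the primary outcome, and that method does not match its own stratified cluster design.

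A second objection is that the analysis sentence speaks of comparing rates between ICUs and might mean an analysis of ICU-level rates. On that reading the type I error problem goes away, but the stratum is still left out.

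A third is that the power contrast compares two clustered analyses, neither of which the protocol contains. That is correct. The figures show what adjustment could add after the clustering fault is repaired; they do not describe the test as written.

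Three stronger readings are tempting and are not supported:
- A reader might infer that the quoted test has error bars that are too wide because of unexplained between-ICU variance. At patient level they are too narrow. The loss of precision arises only in a clustered analysis.
- A reader might infer that each ICU's prior mortality is already known to the sponsor. The document gives one pooled rate from one hospital.
- A reader might infer that adjustment would rescue the power. That requires a correlation for which the document offers no evidence, and at 0.3 the gain is only about 2 points.

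**Conclusion.** The point holds in a limited form. The stated primary test omits both the ICU and the randomisation stratum. The missing ICU term is the graver fault, because it concerns validity. The missing stratum costs efficiency in an otherwise valid clustered analysis.

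Including the stratum is well founded, because the design already uses it. Including prior mortality is a sensible option, conditional on the data. The plausible gain runs from about 2 points of power (r = 0.3) to about 24 (r = 0.8), and the result would still fall well short of 80%.

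These sizes rest on the plan's ICC of 0.01, equal cluster sizes, a 9 to 9 split and an assumed r. Unequal ICU sizes would lower power further. The prior-mortality part also presumes that mortality stays primary; Determination of Sample Size allows the primary outcome to change after the pilot, for example to time to detection.

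**What to change.** 1. Replace the proportional test by a cluster-level analysis or a mixed model with small-sample degrees of freedom, and report the risk difference.
2. Include the ventilator-use randomisation stratum. This needs no new data, because the strata cannot be formed without ventilator-use figures for every unit.
3. Add each unit's pre-trial in-hospital mortality if unit-level rates can be extracted at all three hospitals. Fix the look-back window in advance and state whether the detection system was in use during it. The pilot runs at NTUH in 2025, and Prior Work describes the system as already deployed without giving a date.
4. For secondary outcomes use the same clustered approach with the stratum. Use prior mortality only where it is relevant to the outcome; nothing in the document suggests that it predicts, for instance, time to detect a misplaced tube.
5. Fix these choices before outcome data are seen; collection is planned from January 2026.

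Cost: revised analysis wording, one data extract, and one or two degrees of freedom (under 1 point of power).
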